### Data Collection and Management

#### Plans for Assessment and Collection of Outcomes

Data will be collected at prerandomization, during the sessions, 1 week after the last session before starting the online intervention, after 4 weeks of online intervention, and then at 3- and 12-month follow-ups. Baseline assessment, posttreatment assessment, and follow-up assessments will be completed online. At the beginning of the exposure session, participants will fill in the primary measure again using a paper-and-pencil questionnaire format, and in-session assessments will be filled in the paper session protocol as well. All questionnaires will be based on participants’ self-report. The full timeline of assessments is provided in Table 1.

**Table 1. T1:** Schedule of enrollment, interventions, and assessments for the randomized controlled trial comparing 1-session and 3-session of virtual reality (VR) exposure therapy for public speaking anxiety among young adults.

Assessment/activity	Screening		Postrandomization						Follow-up	
	*t* _−1_ ^a^	*t* _0_ ^b^	*t* _1_ ^c^			*t* _2_ ^d^	*t*_3_-*t*_6_^e^	*t* _7_ ^f^	*f* _1_ ^g^	*f* _2_ ^h^
			Pre-VR exposure	During exposure	Post-VR exposure				3 months	12 months
Informed consent	✓		✓							
Demographic data	✓									
LSAS-SR^i^	✓					✓		✓	✓	✓
PSAS^j^	✓		✓			✓		✓	✓	✓
BFNE^k^	✓					✓		✓	✓	✓
PHQ-9^l^	✓									
IPQ^m^					✓					
In-session assessments: SUDS^n^, catastrophic belief expectancy, quality of performance, single-item presence measure				✓						
Evaluation of intervention format (1-session or 3-session)					✓					
Treatment satisfaction, negative effects								✓		
VR exposure therapy				✓						
4-week online program							✓			
Eligibility criteria	✓	✓								
Treatment expectancy	✓									
Treatment engagement							✓			

a *t*_−1_: online eligibility screening and control data collection (baseline).

b *t*_0_: further screening during telephone interview.

c *t*_1_: face-to-face VR exposure intervention delivery, either via one 3-hour session or via three 1-hour sessions.

d *t*_2_: outcome assessment 1 week after completion of face-to-face VR exposure intervention, either after one 3-hour session or after three 1-hour sessions (first primary endpoint).

e *t*_3_-*t*_6_: 4 weeks of online program with new tasks and materials available weekly.

f *t*_7_: outcome assessment after finishing the 4-week online program or equivalent time if the online program was discontinued (second primary endpoint).

g *f*_1_: follow-up in 3 months after finishing the online program or equivalent time if the online program was discontinued.

h *f*_2_: follow-up in 12 months after finishing the online program or equivalent time if the online program was discontinued.

i LSAS-SR: Liebowitz Social Anxiety Scale – Self-Report.

j PSAS: Public Speaking Anxiety Scale.

k BFNE: Brief Fear of Negative Evaluation Scale.

l PHQ-9: Patient Health Questionnaire-9.

m IPQ: Igroup Presence Questionnaire.

n SUDS: Subjective Units of Distress Scale.

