### Statistical Analysis

The primary outcome will be a change in PSAS scores from baseline to posttreatment assessment (two primary endpoints: *t*_2_ and *t*_7_), as well as during follow-up assessments in both intervention groups. Secondary outcomes will be changes in secondary outcome measures from baseline to posttreatment and follow-ups. Repeated measures within-between ANOVA and effect sizes will be used to assess and compare outcomes within and between groups. The reliable change index (RCI) will be used as a supplementary analysis to analyze individual outcomes following intervention. No interim analyses or formal stopping rules were planned because this intervention is considered low-risk and is not expected to cause any harm to the participants. Regression analysis will be used to test the extent to which the level of anxiety and other psychological states measured by primary and secondary measures during baseline, sense of presence (IPQ at the end of the treatment), age, and gender, and user experience rated by participants predict the efficacy of the intervention. Single-item sense of presence after each task and user experience ratings of the format will be used for further exploratory purposes. In order to handle protocol nonadherence and missing data, it is planned that intention-to-treat will be the primary analysis approach, supplemented by additional per-protocol analysis. As recommended by the CONSORT (Consolidated Standards of Reporting Trials) guidelines, both analyses will be performed and reported for primary outcomes [57], allowing comparison of the effects of both approaches. Multiple imputation techniques will be used to fill in missing data.

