### Ethical Considerations

The trial was approved by the Committee on Research Ethics in Psychology at Vilnius University on November 13, 2023, no. 21/(1.13 E) 250000-KT-166 Vilnius. All participants will be informed about the study conditions and will have to sign an informed consent form before participating in the study.

Informed consent will be collected using an online form before starting the initial screening. Additional written informed consent to participate in the intervention will be obtained face-to-face before the beginning of the VR exposure sessions by the researcher conducting the session. Participants will provide their contact information—email and telephone number—which will be stored in a secure server that will be available to access only to the research team after logging in to the platform. Each participant will have a generated ID number that will be used for appointment scheduling and as a stable identifier in the database across measurements. Signed informed consent forms that also include the name of the participant and contact information will be stored in a locked safe that can only be accessed by one of the team members.

The day-to-day operations will be overseen by the principal investigator with the support of the Lithuanian research team. The trial will receive regular and need-based support from Swedish and Belgian researchers who have vast experience in online-based interventions and VR applications for treating various psychological issues. In case of a need for major changes in the trial protocol, these changes will be reviewed and approved by the institution’s Research Ethics Committee before being implemented. No separate data monitoring committee will be appointed in this study. Participants’ experiences and fidelity to the protocol in the course of face-to-face sessions will be discussed weekly and reported by therapists performing the sessions during the supervision meetings. During the online intervention, participants will be instructed to contact the program’s therapists in case of a deteriorating psychological condition. During the period of data collection, the principal investigator will meet weekly with the research team and the therapists to review the progress and discuss any issues.

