## Discussion

### The Importance of Different Formats

This study will aim to test whether 1-session VR exposure effectiveness for public speaking anxiety differs from the same amount of exposure tasks divided into 3 sessions over the period of 2 weeks, while both programs include 4 weeks of online intervention after the exposure sessions. We consider this study to address an important and practical question regarding the optimal arrangement of VR exposure therapy delivery for public speaking anxiety. A few previous studies found that one VR exposure session [25,43] and 4 sessions of VR exposure therapy [42] were effective in reducing public speaking anxiety. However, to our knowledge, no previous study directly compared the same exposure tasks performed in 1 session and divided into 3 sessions in the context of VR exposure for public speaking anxiety. One session of exposure therapy might be convenient in some contexts but also might be too intensive and long for traditional therapy settings. Extended VR usage in a short period of time might also introduce additional disadvantages in a 1-session exposure. On the other hand, 1-session exposure therapy might be convenient in some contexts, where the number of possible appointments is limited. In addition, the chances of discontinued treatment are likely to be higher in multiple VR exposure sessions compared to one session. This study will compare exposure tasks divided into 3 shorter sessions and a 1-session VR exposure treatment. The study will test an understudied and clinically important question that could generate preliminary evidence of 1-session versus 3-session VR exposure for public speaking comparison and would have the potential to inform future research into optimizing VR exposure for public speaking. However, given a quite limited and specific sample, results would have to be confirmed in larger and more diverse samples.

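### The main endpoint t2 is dated in two ways, from completing all VR sessions or from the last session, and has no equivalent time for participants who stop early or never start

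*Protocol article*

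**What the plan says.** Footnote d of Table 1 defines t2 as "outcome assessment 1 week after completion of face-to-face VR exposure intervention, either after one 3-hour session or after three 1-hour sessions". The Limitations section uses the same definition when it names t2 as the main primary endpoint and keeps t7 as an additional one.

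Elsewhere the anchor is different. The text under Plans for Assessment and Collection of Outcomes says "1 week after the last session before starting the online intervention". The Abstract, the Sample Size section and the Online Intervention section also count from the last session and do not mention completing the set.

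The later assessments have a fallback. Footnote f defines t7 as "outcome assessment after finishing the 4-week online program or equivalent time if the online program was discontinued", and footnote g reads "follow-up in 3 months after finishing the online program or equivalent time if the online program was discontinued"; footnote h does the same for 12 months. The Sample Size section lists three time points and gives the fallback only to the third.

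On analysis, the Statistical Analysis section states that "it is planned that intention-to-treat will be the primary analysis approach", with per-protocol as a supplement and multiple imputation for missing values. On discontinuation, the Discussion says that "the chances of discontinued treatment are likely to be higher in multiple VR exposure sessions compared to one session", and the Limitations section anticipates dropout after one exposure session.

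**The concern.** An intention-to-treat analysis needs an outcome that is due for everyone randomised, on a date that does not depend on finishing treatment. The authors provide for this at t7, f1 and f2, although only for people who stop the online program. At t2, the endpoint they now rank first, they do not.

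Whether the date depends on completion matters more here than in most trials, because completion means something different in each arm. Someone who attends one session and then leaves has completed VR in the 1-session arm but not in the 3-session arm. Under footnote d, the same behaviour gives a t2 date in one arm and none in the other.

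Non-starters are also possible. Under Implementation, allocation follows the phone interview, whereas under Ethical Considerations "Additional written informed consent to participate in the intervention will be obtained face-to-face before the beginning of the VR exposure sessions". A person can therefore be randomised and never reach a session.

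If t2 is lost more often in one arm, among people who leave because of distress or burden, the comparison drifts towards completers. Imputation under missing-at-random repairs this only so far as the observed data explain the loss.

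**Working it through.** **1. Which participants have a t2 date under each wording**

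| Participant | Completion wording (footnote d, Limitations) | Last-session wording (Abstract, Sample Size, Online Intervention, data-collection text) |
|---|---|---|
| 1-session arm, finishes the session | dated | dated |
| 1-session arm, stops partway through | no clear date | dated |
| 3-session arm, attends all three | dated | dated |
| 3-session arm, leaves after session 1 or 2 | no date | dated, if last means last attended |
| Either arm, attends none | no date | no date |

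The two wordings disagree for early stoppers. Neither covers non-starters. The fallback in footnotes f to h does not help, because it applies to stopping the online program. The Online Intervention section also opens that program only after the t2 assessment, so a person with no t2 date has no clear starting point for the later visits.

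**2. The plan's own figure**

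Inputs from Sample Size: f = 0.25, m = 3 time points, correlation 0.5, alpha 0.05, two groups, N = 86. For the between-groups effect:

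lambda = f² × N × m / (1 + (m − 1) × rho) = 0.0625 × 86 × 3 / 2 = 8.06, with 1 and 84 degrees of freedom.

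Power is 0.801 at N = 86 and 0.792 at N = 84, so 86 is reproduced. The section states no allowance for dropout. With two groups, f = 0.25 corresponds to 2 × 0.25 = 0.5 SD.

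**3. Illustration of size (assumed inputs)**

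The article gives no VR discontinuation or t2 loss rate. Assume 43 per arm, 5% loss of t2 in the 1-session arm (43 × 0.95 = 40.9 observed), and 10%, 20% or 30% loss in the 3-session arm. Assume also that those lost would have scored 0.3 to 0.8 SD worse than those observed.

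- Effective N = 4 × n1 × n3 / (n1 + n3)
- Complete-case bias = (loss in 3-session arm − loss in 1-session arm) × gap, with no true difference

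| Loss, 1 v 3 sessions | Observed, 1 v 3 sessions | Effective N | Power | Bias at gap 0.3 / 0.5 / 0.8 SD |
|---|---|---|---|---|
| 5% v 10% | 40.9 v 38.7 | 79.5 | 0.77 | 0.015 / 0.025 / 0.04 |
| 5% v 20% | 40.9 v 34.4 | 74.7 | 0.74 | 0.045 / 0.075 / 0.12 |
| 5% v 30% | 40.9 v 30.1 | 69.3 | 0.71 | 0.075 / 0.125 / 0.20 |

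The bias favours three sessions, given the assumed direction of the gap. Relative to 0.5 SD it runs from 0.015 / 0.5 = 3% to 0.20 / 0.5 = 40%.

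**4. How few people this takes**

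The Results section reports 37 randomised by November 2025, about 18 per arm under equal allocation. Losing two to five people from one arm would be 2/18 = 11% to 5/18 = 28%.

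**The case against.** The strongest counter-argument is that the document never withholds t2 from anyone. It is an online questionnaire. Missed sessions are followed up by phone and rescheduled where possible, people who discontinue are contacted, reminders go out by email and then phone, and reasons for discontinuation are recorded. Four places time t2 from the last session, which for a partial completer can be read as the last one attended. Stopping treatment is also not the same as failing to return a questionnaire: the Discussion predicts the first and is silent on the second. Participants confirm beforehand that they can attend and are not told that session number is under test, so refusal prompted by allocation is speculative.

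Most of this stands. A reader might infer that t2 is missing by design for non-completers, or that the intention-to-treat analysis will in fact lose its outcome mainly in the 3-session arm. The documents do not support either statement; uneven loss is a foreseeable risk and no more. The bias figures are complete-case arithmetic, and the planned multiple imputation could explain part of the gap from observed scores.

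Three things remain. The two wordings conflict for early stoppers, and no wording dates t2 for non-starters. The follow-up contacts are aimed at continuing treatment or at follow-up questionnaires and set no t2 date. Nor is this a detail that an article would leave to a fuller document: the article gives the schedule itself, with the fallback stated for three other assessments.

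It can also be said that the remedy comes late, since the Limitations section reports that the team has already worked with data. That limits the remedy for t2 dates already past, but reporting and sensitivity analysis remain possible.

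**Conclusion.** The point holds as an inconsistency and a gap in the definition of the main endpoint. Early stoppers have a t2 date under one wording and not under the other; randomised participants who attend no session have none. If footnote d is applied literally, t2 could be lost unevenly in the 3-session arm, where the protocol itself expects more discontinuation, and imputation under missing-at-random may not correct that.

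The size is unknown, because no dropout rate is given and the documents do not show which wording was followed in practice. The 0.015 to 0.20 SD range rests on three assumptions: the loss rates, the gap between lost and observed participants, and a complete-case analysis. It shows what uneven loss could do; it does not estimate what happened. The planned N of 86 is reproduced and is not in question.

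**What to change.** Reconcile footnote d and the Limitations text with the last-session wording, and state one rule: t2 is due for every randomised participant who has not withdrawn consent to questionnaires, 1 week after the last VR session attended or, for those attending none, at the equivalent scheduled time from randomisation for their arm. The article gives no interval from randomisation to first session, so the team must supply it. They should also confirm that the online screening consent covers questionnaires after randomisation before approaching people who did not sign the second consent.

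For participants already past t2, report t2 missingness by arm with reasons, separating early stoppers from non-starters, and say which dating rule was followed. Add a delta-adjusted imputation sensitivity analysis that shifts the imputed t2 scores over a stated range, with shifts allowed to differ by arm. Label it as added after data were seen.

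The cost is a line in the schedule, a few extra questionnaire reminders and a little more analysis work. If the team regards the rule as a major change, the protocol's own procedure sends it to the ethics committee first.

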#### Plans to Promote Participant Retention and Complete Follow-Up

Participants will be informed about the follow-up assessments prior to the study. Participants will need to confirm that they are willing and able to participate in face-to-face sessions and online intervention before being included in the study. Simple reminders to fill out the follow-up questionnaires will be sent by email, followed by a phone call. In case participants discontinue the intervention, team members will contact them to first address any concerns that might be interfering with the intervention continuation.

#### Data Management

All of the data will be collected and stored on a secure, encrypted server of the Iterapi platform [56]. For data analysis, data will be kept on password-protected team members’ computers. Personal data like contact information will only be stored throughout the duration of the study and follow-ups.

### Statistical Analysis

The primary outcome will be a change in PSAS scores from baseline to posttreatment assessment (two primary endpoints: *t*_2_ and *t*_7_), as well as during follow-up assessments in both intervention groups. Secondary outcomes will be changes in secondary outcome measures from baseline to posttreatment and follow-ups. Repeated measures within-between ANOVA and effect sizes will be used to assess and compare outcomes within and between groups. The reliable change index (RCI) will be used as a supplementary analysis to analyze individual outcomes following intervention. No interim analyses or formal stopping rules were planned because this intervention is considered low-risk and is not expected to cause any harm to the participants. Regression analysis will be used to test the extent to which the level of anxiety and other psychological states measured by primary and secondary measures during baseline, sense of presence (IPQ at the end of the treatment), age, and gender, and user experience rated by participants predict the efficacy of the intervention. Single-item sense of presence after each task and user experience ratings of the format will be used for further exploratory purposes. In order to handle protocol nonadherence and missing data, it is planned that intention-to-treat will be the primary analysis approach, supplemented by additional per-protocol analysis. As recommended by the CONSORT (Consolidated Standards of Reporting Trials) guidelines, both analyses will be performed and reported for primary outcomes [57], allowing comparison of the effects of both approaches. Multiple imputation techniques will be used to fill in missing data.

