### Sample Size

Sample size was calculated for superiority analysis to test whether one condition shows bigger effects at least at the medium effect level. Power analysis was performed using the G*Power program for repeated measures ANOVA between factors’ effects, which showed that given a significance level of .05 to achieve 80% power to detect a medium between-groups effect (Cohen *f*=0.25) with 2 groups × 3 time measurements (pretreatment, 1 week post last exposure session, and at the end of the online intervention period or equivalent time), with an estimated correlation between repeated factors of 0.5, a total sample of 86 is needed.

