Another limitation is that the original protocol version did not detail some of the statistical analysis plans such as handling of sphericity/normality violations, missing data, and multiple imputation model variables, and correction for multiple comparisons. Repeated measures ANOVA might not be the most suitable analysis for the study questions, and a more robust method such as linear mixed effects modeling could be a more appropriate statistical analysis. Moreover, the initially planned multiple primary endpoints have been deemed complicated; thus, *t*_2_ (ie, outcome assessment 1 week after completion of face-to-face VR exposure intervention, either after one 3-hour session or after three 1-hour sessions) is now being considered as the main primary endpoint because the assessment is performed following different conditions, while *t*_7_ remains an additional primary endpoint. We could not add these to the protocol’s statistical analysis plan because this was pointed out by the reviewers after the research team had already seen and worked with the data. These final statistical decisions, including considerations to include more robust analysis methods, will be described in the reports of the study results.

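### The planned ANOVA treats baseline as a time level and names no t2 or t7 contrast; add baseline-adjusted arm differences, labelled post hoc

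*Protocol article*

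**What the plan says.** The Statistical Analysis section defines the outcome as "The primary outcome will be a change in PSAS scores from baseline to posttreatment assessment (two primary endpoints", these being t2 and t7. It then fixes the method: "Repeated measures within-between ANOVA and effect sizes will be used to assess and compare outcomes within and between groups". It names no model term or contrast as the primary test, and no baseline covariate in the comparison of arms.

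The Sample Size section shows how the model is understood: "Power analysis was performed using the G*Power program for repeated measures ANOVA between factors’ effects". The levels entered are two groups by three "time measurements (pretreatment, 1 week post last exposure session, and at the end of the online intervention period or equivalent time", so pretreatment is an outcome level.

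The Limitations section concedes that "Repeated measures ANOVA might not be the most suitable analysis for the study questions" and that a linear mixed model could be more appropriate. It says t2 is now considered the main primary endpoint, with t7 as an additional one. It explains that the plan could not be altered because the team had already worked with the data, and leaves final decisions to the results report. It mentions neither baseline adjustment nor a contrast at t2.

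**The concern.** The question is whether the arms differ in PSAS at t2, and again at t7. Neither omnibus term of a two-by-three ANOVA with baseline as a level answers it. The group term mixes in a time point before any treatment. The interaction asks only whether the pattern over time differs somewhere. Making t2 the main endpoint widens the gap between question and test.

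Three things are at stake. The report may lead with a p-value that carries no arm difference at the named endpoint. The 80% power attaches to a term that is diluted when the effect arises only after baseline. And the baseline score, already collected, is not used as a covariate, which under the plan's own inputs costs precision. Leaving the choice of model open after data access also leaves more analytic freedom than naming one model now.

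**Working it through.** **Inputs.** From Sample Size: alpha 0.05, 80% power, Cohen f=0.25, 2 groups, 3 times, correlation ρ=0.5, N=86. For two equal groups d=2f=0.5. Allocation is equal (Allocation section). Baseline is the screening PSAS (Primary Outcome Measures). Entry requires PSAS of 60 or above (Eligibility Criteria) on a scale of 17 to 85. By November 2025, 37 had been randomised (Results). My assumptions: complete data, a common correlation, and equal SDs except where varied. Effects are in units of the t2 SD.

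**Step 1: the plan's own figure.** For the between-groups term, λ = f²·N·m/(1+(m−1)ρ) = 0.0625×86×3/2 = 8.06 on 1 and 84 df. Power is 80.1%; at N=84 it is 79.2%. The stated 86 reproduces.

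**Step 2: the same term with no difference at baseline.** With arm differences (0, 0.5, 0.5) the average is 0.333. The variance of a participant's mean is (1+2×0.5)/3 = 0.667. Then λ = 0.333²/(4×0.667/86) = 3.58, and power is 46.5% (20,000 simulated trials: 46.5%). For the average to reach 0.5, the difference at both t2 and t7 would have to be 0.75, since (0+0.75+0.75)/3 = 0.5.

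**Step 3: the interaction.** λ = (N/4)·Σ(δ−δ̄)²/(1−ρ). For (0, 0.5, 0.5), Σ = 0.167 and λ = 21.5×0.167/0.5 = 7.17 on 2 and 168 df, giving power 65.8%. The patterns (0, 0.5, 0) and (0, 0, 0.5) have the same Σ and so the same λ. The test responds identically to an effect at t2 only, at t7 only, or at both.

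**Step 4: the contrast at t2.** The noncentrality is 0.5/√(4V/86).
- t2 score alone, V=1: 2.318, power 63.0%.
- Change from baseline, V=2(1−ρ)=1: 2.318, power 63.0%.
- Adjusted for baseline, V=1−ρ²=0.75: 2.677, power 75.4% (simulated 74.7%).

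The gain is 12.4 points over the change score and 9.6 over the interaction. At the 37 randomised so far, the figures are 31.6% (change), 31.7% (interaction) and 40.0% (adjusted).

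**Step 5: how far the gain depends on the inputs.** Let k be the baseline SD divided by the t2 SD. The change score has V=1+k²−2ρk; the adjusted contrast keeps V=1−ρ². At N=86:

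| k | ρ | Change | Adjusted | Gain (points) |
|---|---|---|---|---|
| 1 | 0.3 | 49.1% | 67.1% | 18.0 |
| 1 | 0.5 | 63.0% | 75.4% | 12.4 |
| 1 | 0.6 | 72.7% | 81.7% | 9.1 |
| 1 | 0.7 | 84.1% | 89.4% | 5.3 |
| 1 | 0.8 | 95.2% | 96.8% | 1.7 |
| 0.75 | 0.5 | 72.0% | 75.4% | 3.4 |
| 0.5 | 0.5 | 75.4% | 75.4% | 0.0 |

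The values of k below 1 are assumptions. The documents give no SDs, but an entry threshold of 60 on a scale ending at 85 makes compression of the baseline plausible. Under the same compression, with d=0.5 at both t2 and t7 and ρ=0.5, the interaction's simulated power is about 74% at k=0.75 and 78% at k=0.5 (40,000 runs, no sphericity correction). The advantage over the interaction can therefore vanish or reverse.

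**The case against.** The strongest reply is that the authors already concede the general point and declined to rewrite the plan after seeing data, which is the disciplined course. That stands: the absence of a mixed model from the plan is not the criticism. What the concession leaves open is the contrast and the baseline adjustment.

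Second, a reader might infer that the planned ANOVA cannot yield a t2 comparison at all. The documents do not support that. A planned contrast, or a two-by-two ANOVA on baseline and t2 whose interaction is the change-score test, lies within the stated method, and such detail is often left to a fuller plan. The criticism applies to the omnibus terms only.

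Third, the diluted group term is the one used for sizing; the Statistical Analysis section does not call it primary. This is correct, so the 46.5% describes what the sample size delivers for that term, not the power of a declared primary test.

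Fourth, a reader might count it a defect that "Multiple imputation techniques will be used to fill in missing data". It is not: under missing at random, imputation is an accepted route to intention-to-treat, and a likelihood-based model is an alternative, not a correction.

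Finally, a new model chosen after data access is not free. It carries a credibility cost that only disclosure can meet.

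**Conclusion.** The concern holds in a limited form. The plan names neither the arm difference at t2 nor that at t7 as the estimate. The term it sized has 46.5% power at N=86 if d=0.5 exists only after baseline, and the omnibus interaction cannot locate a difference. A baseline-adjusted contrast answers the stated question directly. Apart from one degree of freedom, it is at least as efficient as the change score.

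A power gain of 9 to 12 points should not be quoted without its conditions: d=0.5, ρ near 0.5 to 0.6, equal SDs, N=86 and complete data. Step 5 shows it can fall to nothing. Nor can a gain be stated for the realised sample, because recruitment was still open at 37 randomised and the final number is not given. The case for the change rests first on matching the estimate to the endpoint, and only second on power.

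**What to change.** State the arm differences in PSAS at t2 (main) and at t7 as the estimates. Report each with a 95% CI from a model adjusted for screening PSAS. Either of these would serve:
- an ANCOVA at each time; or
- a mixed model with arm, time, arm-by-time, baseline and baseline-by-time, with a small-sample degrees-of-freedom correction.

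Place the results beside the planned ANOVA, not in its stead, and say plainly that the adjusted analysis was adopted on design grounds after the data had been accessed. Multiple imputation can stay as planned.

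The cost is a modest extra analysis, a paragraph of text and the open admission that the analysis is post hoc. No further participants or measurements are needed.
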